## Background

Despite the proliferation of mobile health (mHealth) programs, evidence on their effectiveness is limited [1, 2]. mHealth solutions which provide stage-based health information messages to pregnant and postpartum women have been shown to increase knowledge, as well as the utilization of antenatal care (ANC), skilled birth attendance (SBA), and childhood immunization rates in Malawi and Zanzibar [1, 3, 4]. However, efforts to compare and/or generalize these findings are limited by the paucity of data and the quality of evaluations and evidence reporting. To date, none of the summative evaluations have reported data on exposure—defined as a function of whether users receive content (technological performance) and how they engage with that content (behavioral performance)—thus hindering efforts to understand the casual pathways between program inputs and the summative outcome measures observed [3, 5, 6].

Despite evidence limitations, maternal messaging programs are among the few examples of mHealth programs which have been successfully scaled. In four countries globally, programs exist with over one million beneficiaries: *Aponjon* in Bangladesh, *mMitra* and *Kilkari* in India, *Wazazi Nipendeni* in Tanzania, and *MomConnect* in South Africa [7]. As these programs transition from donor funding to full integration with public sector health services, renewed calls to generate evidence on their effectiveness and value for money are emerging.

In India, the Kilkari program is an outbound service that delivers weekly, stage-based audio messages about pregnancy, childbirth, and childcare directly to families on their mobile phones, starting from the second trimester of pregnancy until the child is one year old. Initiated in Bihar in 2012, Kilkari has been scaled to 13 states across India with support from Ministry of Health and Family Welfare (MOHFW) at the national level, National Health Missions (NHM) at the state level, and an alliance of donors (Bill and Melinda Gates Foundation, US Agency for International Development (USAID), Barr Foundation, and UK Department for International Development (DFID)). In the preceding 33 months, Kilkari has delivered pre-recorded audio content to an estimated 8.3 million users—making it the largest maternal messaging initiative underway globally.

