### Allocation and randomization

Gestational age, parity, age of woman, and ownership of phone are important variables potentially associated with exposure (listening to messages) and are likely to influence outcomes. The sample will be stratified by the above variables to allow for equal numbers of these categories in the sample between intervention and control groups (balance of covariates in the sample). Randomization will be performed using the *sample* command in stata with the use of the above listed variables as stratifiers. The randomization procedure will be done in blocks (block randomization) after the enrollment is completed for each sub-district administrative unit called as Community Development Block. This is to ensure a similar number of intervention and control subjects for each Community Development Block.

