#### Study aim 4: Determine whether users are listening to calls received

To measure user engagement with Kilkari content (behavioral performance), we will measure the proportion of calls listened to out of those received on average among the mobile phones enrolled to Kilkari. MOTECH data will be merged with IVR, call center data, and baseline face to face survey data on user characteristics, including socioeconomic status, education, phone access, mobile literacy, and numeracy, and used to identify predictors for exposure to Kilkari content. Differentials in listening patterns for each mobile device will be used to classify Kilkari users into high and low listenership groups. In addition to quantitative data analyses, qualitative interviews will be carried out to examine user perceptions of mobile messaging and use of data for program design and decision-making. Differentials in user perceptions of content by topical area as well as over time will be assessed to facilitate understanding of possible differentials in user engagement.

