### Analyses

The statistical analysis plan will ensure that the analyses are not data driven or selectively reported. The presentation of primary analyses is expected in spring 2020, after all participants have been followed up to 1 year postpartum. Unadjusted and adjusted results will be presented as appropriate effects sizes with 95% confidence intervals (CI). Demographic and population characteristics of the women at baseline will be compared between study groups. Significance tests will be performed to investigate for differences between groups at baseline. Categorical outcomes will be analyzed using contingency tables and chi-square test. Continuous normally distributed variables will be analyzed using *t*-tests and non-normally distributed variables using non-parametric tests. The primary outcomes, early and exclusive breastfeeding and the adoption of modern contraception at 1 year postpartum, will be analyzed by intention-to-treat methodology, with adjustment for stratifying and baseline factors, including gestational age at enrollment, ownership of mobile phone, age of the pregnant woman at enrollment, and birth order of index pregnancy. Binary logistic regression (BLR) models with generalized estimation equations will be used to account for clustering effects at the level of the Community Development Block. The secondary outcomes of interest are anticipated to include immediate breastfeeding, skilled attendance and facility delivery, postnatal care, newborn birth practices, and immunizations. Binary logistic regression will be used for binary outcomes, and multiple linear regression will be used for continuous measures. Wilcoxon rank sum test will be used for continuous measures which are not normally distributed, including duration of breastfeeding. Cox proportional hazards regression will be used for time to event analyses, including time to initiation of breastfeeding and adoption of a modern contraceptive method in the postpartum period. All regression analyses will be performed with adjustment for baseline factors.

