Comparisons between the treatments will be performed in pre-specified subgroups, including phone ownership, caste, age groups, etc. The subgroup analysis does not comprise the primary analysis and did not inform the sample size calculation. The interpretation of any heterogeneity in effects due to the subgroups will be based on using interaction terms between the sub-group variables and the intervention group with no adjustment for multiple testing. The exposure of women to different messages will be assessed using the system-generated data from the MOTECH database. We will analyze the effect of different messages on specific related outcomes using a per-protocol methodology. Missing data will be assessed for any systematic biases based on the dropout of women using their baseline characteristics. Sensitivity analysis will be performed to assess the effect of different levels of systematic bias on the effect sizes.

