### Limitations

As part of this study, the evaluation team will facilitate the identification and enrollment of pregnant women to Kilkari. The timing of this enrollment is intended to mirror that observed in other state deployments of Kilkari which rely on the identification of pregnant women via the MCTS/ RCH health information system databases, and in practice, therefore, enroll women in the later stages of pregnancy and/or early postpartum. By facilitating the enrollment of women directly into Kilkari, we anticipate having significantly higher population level coverage than the program would otherwise garner had enrollment relied on women identified via routine health information systems maintained by public sector providers. In addition, user listening patterns among trial participants may differ from those observed amongst Kilkari users in other states given that trial enrollment occurred through a face to face interaction—a factor which may lead to greater rapport building and in turn improved user engagement with the program. The question of generalizability is an issue to contend with since the study takes great efforts to provide correct phone numbers for the enrolled women, unlike the usual MCTS/RCH registration system. Higher population level coverage could lead to differences in the characteristics of women enrolled in the study compared to those enrolled through routine health information systems, resulting in selection bias. The measurement of outcomes is based completely on self-reports as part of household surveys. This can result in information bias due to recall issues and a social desirability to report ‘appropriate’ behavior and practice. The use of a RCT design is expected to limit the role of confounders but cannot be entirely ruled out.

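### The planned per-protocol analysis of message effects conditions on exposure seen only after randomization, so it is a non-randomized comparison open to bias of several points

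*Protocol article*

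**What the plan says.** All references are to the protocol article.

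- **Analyses**, on the source of exposure: "The exposure of women to different messages will be assessed using the system-generated data from the MOTECH database". The next sentence fixes the method: "We will analyze the effect of different messages on specific related outcomes using a per-protocol methodology". The per-protocol population, the exposure threshold and the comparator are not given.
- **Background** treats exposure as two things together: whether content reaches the user, and how the user engages with it.
- **Study aim 4** (Measurement): "Differentials in listening patterns for each mobile device will be used to classify Kilkari users into high and low listenership groups". No cut-off is given, and this paragraph describes no outcome comparison between the groups.
- **Allocation and randomization** says that gestational age, parity, age and phone ownership "are important variables potentially associated with exposure (listening to messages) and are likely to influence outcomes".
- **Analyses**, on the safeguards: the primary outcomes "will be analyzed by intention-to-treat methodology", and "All regression analyses will be performed with adjustment for baseline factors".
- **Limitations**, on confounding: "The use of a RCT design is expected to limit the role of confounders but cannot be entirely ruled out". The remark concerns the design as a whole and does not mention the exposure analysis.

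**The concern.** Randomization makes the two arms comparable as wholes. It does not make the women who received and engaged with calls comparable with anyone else. Exposure arises after allocation, and controls, who are sent no calls, have no counterpart record from which a matching subgroup could be picked. The protocol names variables that it thinks drive both listening and outcomes, so the conditions for selection bias are ones the authors already accept.

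Timing may add to this. The intervention description places 24 calls in the first 6 months postpartum and 24 more from 6 to 12 months, the same periods in which exclusive breastfeeding and contraceptive uptake are determined. A woman who has stopped exclusive breastfeeding may lose interest in the calls. Adjustment for baseline factors cannot remove that.

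At stake is the reading of the exposure-outcome link, which the Abstract and Discussion present as a distinctive contribution of the trial. Objective 5b also speaks of women exposed versus not exposed. That may simply mean the two arms. If it means listeners, the same bias would pass into the cost per DALY averted.

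**Working it through.** **Plan's own figure.** The document gives no number for the per-protocol analysis. The yardstick is the 5% difference in the Sampling section, read here as 5 percentage points on a 58% control rate. For 58% versus 63%, two-sided alpha 0.05 and 80% power, I get 1500 per arm, or 3000 in total (3080 with continuity correction), against the stated 3200. The step 3200 x 1.25 / 0.80 = 5000 reproduces the enrolment figure. The gap between 3000 and 3200 has no bearing on this point.

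**Inputs from the plan.** Control rate 58%; target 5 points; enrolment 5000; loss to follow-up 20%; design effect 1.25; equal arms (taken from the aim of similar numbers per Community Development Block).

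**Assumed inputs.** f is the share of the intervention arm counted as exposed. g is the outcome gap between exposed and unexposed women in that arm that would exist without any message effect and that remains after baseline adjustment. The document gives neither, so ranges are shown.

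**Bias if the comparator is all controls.** Let the exposed have rate pL, the unexposed pN, and controls m. With no message effect, randomization gives f x pL + (1 - f) x pN = m in expectation. With g = pL - pN,

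pL - m = g x (1 - f).

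Setting this to 5 points gives g = 5 / (1 - f):

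| f | g needed | Exposed vs unexposed rates | Odds ratio |
|---|---|---|---|
| 25% | 5 / 0.75 = 6.7 points | 63.0% vs 56.3% | 1.32 |
| 50% | 5 / 0.50 = 10 points | 63% vs 53% | 1.51 |
| 75% | 5 / 0.25 = 20 points | 63% vs 43% | 2.26 |

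For fixed gaps:

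| f | Bias, g = 5 points | Bias, g = 10 points |
|---|---|---|
| 25% | 3.75 | 7.5 |
| 50% | 2.5 | 5.0 |
| 75% | 1.25 | 2.5 |

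**Chance of a false positive.** Analysed per arm: 5000 x 0.80 / 2 = 2000. Effective size: 2000 / 1.25 = 1600 controls against f x 1600 exposed women (400, 800, 1200). With no message effect, the chance of p < 0.05 for f = 25%, 50% and 75% is 78.6%, 65.4% and 26.4% when g = 10 points, and 27.3%, 21.5% and 9.7% when g = 5 points. The nominal level is 5%.

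**Bias if the comparator is low listeners.** The difference is pL - pN, so the whole of g appears, whatever f is.

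**The assignment-based alternative.** The complier-average estimate is the intention-to-treat risk difference divided by the difference between arms in the share exposed. With no message effect the numerator is zero in expectation, so g does not enter. The price is precision: if controls are unexposed, the standard error is roughly the intention-to-treat one divided by f, that is 4 times at f = 25%, 2 times at 50% and 1.33 times at 75%.

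**The case against.** **The comparator and threshold are not stated, and definitions commonly sit in an analysis plan that is not shown.** This stands in part. A reader might infer that the plan commits to comparing listeners with all controls. It does not say so; that is only the usual reading of per protocol. But the point is not the missing definition. The article states the method and the post-randomization exposure variable, and neither natural comparator restores randomization.

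**Adjustment is planned.** This stands, and it is why g must mean the residual gap. The named stratifiers are adjusted for, and under Study aim 4 the system data will be merged with baseline socioeconomic status, education, phone access, mobile literacy and numeracy. What may remain is motivation, day-to-day control of the phone, and listening that responds to the outcome.

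**Non-receipt is partly technical.** This also stands. Network variation or an inactive number is not the same as choosing not to listen, and a receipt-based definition might carry a smaller g. Engagement is nevertheless part of the protocol's definition of exposure.

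**The size rests on inputs the document does not give.** This stands. With a 5-point gap, no value of f produces a 5-point bias, and at 75% exposed a 20-point gap is required.

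**The high and low listenership groups and the Limitations remark are not errors.** Agreed. A reader might infer that outcomes will be compared between those groups, but Study aim 4 describes them only in the context of engagement and its predictors. The Limitations sentence is candid; it just does not reach this analysis.

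**An instrument cannot answer a question about individual messages.** This stands and limits the remedy. Assignment delivers every topic together (Table 1: family planning 16%, infant feeding 13%, child immunizations 11% and others), so one randomized arm cannot separate them.

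**Conclusion.** The concern holds in limited form. The article commits to estimating message effects by a method that conditions on exposure recorded after randomization and only in the intervention arm, while saying that listening and outcomes share determinants. The result is an observational comparison. Under the all-controls reading, a null effect could appear as 5 points with residual gaps of about 6.7, 10 or 20 points at 25%, 50% or 75% exposed. The first two correspond to modest odds ratios (about 1.3 and 1.5), the last to a large one (about 2.3). A high-versus-low contrast would carry the full gap.

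Two stronger readings are not supported. The documents do not show that a 5-point artefact will occur, because f and g are both assumed. Nor is the trial's main result compromised, because the primary outcomes are analysed by intention to treat. What is exposed is the message-effect analysis and, if Objective 5b is taken to mean listeners, the economic evaluation. This should be corrected, but it does not threaten the primary conclusion.

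**What to change.** 1. Make the causal exposure analysis a complier-average effect of overall Kilkari exposure. Define exposure by a listening threshold from the system data, fixed before outcomes are seen. Use randomized arm as the instrument, work on the risk-difference scale, adjust for the randomization strata, and allow for contamination that controls report in the surveys.
2. State the exclusion restriction: assignment affects the outcome only through exposure as defined. With a threshold, this includes no effect of listening below it, so a second, lower threshold is a useful sensitivity analysis.
3. Do not run the instrument one topic at a time as if topics had been randomized separately. Any topic-specific estimate must state the assumption that other topics do not affect that outcome.
4. Report per-protocol and listener-based message-outcome results as covariate-adjusted, non-randomized associations, with population, threshold and comparator named.
5. Do not use those results as the effectiveness input to the economic evaluation, and say in Objective 5b whether exposed means assigned.

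Cost: wording in the analysis plan and some analysis time. Assignment, system data and contamination questions are already planned. The downsides are wider intervals and an exclusion restriction that cannot be fully tested.

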### Sampling

Table 2 summarizes the sample size requirements by activity, along with underpinning assumptions. To determine changes in RMNCH knowledge, practices, and careseeking over time (study aim 1), sampling will be powered to detect changes in coverage across study arms. To detect a 5% difference in reported practice of exclusive breastfeeding assuming an alpha of 0.05, 80% power, the estimated sample size for a two-sample proportions test would be 3200 women. After adjusting for a design effect (variance inflation factor) of 1.25 due to clustering at the level of the Community Development Block and a 20% loss to follow-up from enrollment to endline surveys and a potential loss of 35% of women due to poor reporting of phone numbers and/or changes to original phone numbers provided, a total of 5000 women will be enrolled to the study. Assuming 40% of women have access to a mobile phone, we anticipate that nearly 700,000 households will be listed in all four districts of MP.

**Table 2 Tab2:** Sample size estimates by study aim

Study aim	Survey	Target population	Sample size	Assumptions
Study aim 1a*	Face to face survey to measure changes in infant feeding practices	Women 5–7 months pregnant in four districts of MP	5000	• 5% change in reported practice of immediate and exclusive breastfeeding • Loss to follow-up of 20% from enrolment to final follow-up visit • Variance inflation factor of 1.25
Study aim 1b	Phone survey to measure changes in infant feeding	Postpartum women randomized to Kilkari	5000	Descriptive survey; administered to all women enrolled into the study
Study aim 1c*	Test-retest	Women 5–7 months pregnant in four districts of MP	168 women to be interviewed twice	• Proportion of positive responses of 0.35 for rater 1 and 0.40 for rater 2 • Adjusting for a 15% loss to follow-up/refusal between the first and second surveys
Study aim 1*	Phone survey for postpartum women: infant feeding, essential newborn care, RMC during childbirth	Women 1–4 months postpartum in two districts of MP	880 women interviewed as part of face to face surveys contacted to yield 146 completed face to face and phone survey interviews	• 20% phone survey response rate • Proportion of positive responses of 0.35 for rater 1 and 0.40 for rater 2

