### Measurement

Figure 2 provides an overview of enrolment and study design over time and the Standard Protocol Items: Recommendations for Interventional Trials (SPIRIT) are presented in Fig. 3 and Additional file 1. At enrollment, women will be administered a survey containing modules on phone ownership, geographical and demographic characteristics, knowledge (danger signs during pregnancy, delivery, and postpartum; essential newborn care; nutrition; hygiene, diarrhea treatment, family planning, etc.), practices (immediate, early, and exclusive breastfeeding; complementary feeding; skin-to-skin care, etc.), RMC, and coverage for antenatal care, delivery, and postnatal care. Around 6–8 weeks after the expected date of delivery, a phone survey will be administered to a random sample of the enrolled women until a target sample size of 3500 is attained (1750 each in intervention and control arms) to assess breastfeeding and newborn care practices. An endline survey will be carried out from November 2019 to February 2020 and each woman will be followed up at 12 months postpartum based on their expected date of delivery at enrollment. The endline survey will capture data on practices during pregnancy and intrapartum and postpartum periods.

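### Dropout bias is to be judged on baseline characteristics recorded in pregnancy; for the breastfeeding outcomes the postpartum phone-survey answers should be added as auxiliary data

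*Protocol article*

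**What the plan says.** The Analyses section of the protocol article gives two steps for missing data. The first is "Missing data will be assessed for any systematic biases based on the dropout of women using their baseline characteristics". The second is "Sensitivity analysis will be performed to assess the effect of different levels of systematic bias on the effect sizes". It names no variable recorded after baseline and no source for the bias levels.

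The Sampling section plans for "20% loss to follow-up from enrollment to endline surveys" and also mentions a "potential loss of 35% of women due to poor reporting of phone numbers".

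The Measurement section says that, around 6–8 weeks after the expected delivery date, "a phone survey will be administered to a random sample of the enrolled women until a target sample size of 3500 is attained", split 1750 per arm, "to assess breastfeeding and newborn care practices". Under Study aim 1, the phone survey goes to all participants at 1 month postpartum, and the same subsection ends with 1–4 months. Table 2 lists 5000 women for it. The Phone surveys subsection gives these data mainly a reliability purpose.

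The primary outcomes are early breastfeeding, exclusive breastfeeding (0–6 months in the research hypothesis) and modern contraception at 1 year.

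**The concern.** Baseline is taken at 12–34 weeks of gestation. A comparison of dropouts with completers on age, parity, phone ownership and similar variables can show that different kinds of women were lost. It cannot show directly whether women who fed differently were lost, or whether this differed by arm. The trial is unblinded and one arm receives weekly calls, so a difference by arm is conceivable.

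The phone survey comes after birth and before endline. Early initiation is settled by then. Exclusive breastfeeding to 6 months is settled only for women who have already stopped; for the rest, the phone answer is a predictor. For women who answer by phone and are later lost, this is more direct evidence than any baseline variable, and it could also inform the bias levels that the sensitivity analysis must otherwise assume. At stake is how far the breastfeeding effects can be defended when about one woman in five is unseen at endline.

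**Working it through.** **1. The planned loss.** The Sampling section states that "the estimated sample size for a two-sample proportions test would be 3200 women", with a design effect of 1.25, a 20% loss, and that "a total of 5000 women will be enrolled to the study". Check: 3200 × 1.25 ÷ 0.80 = 5000. The 20% is therefore the loss built into the enrolled number: about 1000 women lost and 4000 seen. The 35% phone-number loss is not in the 5000.

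**2. How many lost women have phone answers.** The document does not give this share; call it f. The phone target covers 3500 ÷ 5000 = 70% of women. If phone response is independent of later loss, f = 0.70, or about 700 of 1000. The counts alone (3500 women in the phone survey and 4000 women at endline) allow anything from 0 to 1000. I use f = 0.70, 0.35 and 0.20 as assumptions.

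**3. Complete-case bias.** Assume that lost women in one arm have a prevalence 10 points below retained women, with no gap in the other arm. Bias = 0.20 × 10 = 2.0 points, or 2.0 ÷ 5 = 40% of the target difference.

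**4. What imputation with phone answers leaves.** Take 35% prevalence in retained women (the setting section's figure for breastfeeding within one hour), hence 25% in lost women, and assume that 9% of phone answers disagree with the endline answer.

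- Share of retained women who answer yes in the phone survey = 0.35 × 0.91 + 0.65 × 0.09 = 0.377. Kappa is then 0.81, close to the 0.80 assumed in Table 2.
- Probability of an endline yes after a yes in the phone survey = 0.35 × 0.91 ÷ 0.377 = 0.845. After a no in the phone survey it is 0.35 × 0.09 ÷ 0.623 = 0.051.
- Share of lost women who answer yes in the phone survey = 0.25 × 0.91 + 0.75 × 0.09 = 0.295.
- Imputed prevalence in lost women with phone data = 0.295 × 0.845 + 0.705 × 0.051 = 0.285, against a true 0.25. A gap of 3.5 points remains.
- Lost women without phone data keep the full 10-point gap.

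Residual bias = 0.20 × [3.5f + 10(1 − f)]:

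| f | Residual bias (points) |
|---|---|
| 0 | 2.0 |
| 0.20 | 1.7 |
| 0.35 | 1.5 |
| 0.70 | 1.1 |

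If the phone answer stood in perfectly for the outcome, 2.0 × (1 − 0.70) = 0.6 would remain at f = 0.70.

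**5. Weaker prediction, as for exclusive breastfeeding.** In this set-up the residual equals 2.0 × (1 − f r²), where r is the correlation of phone and endline answers; the 9% disagreement gives r = 0.81. With r = 0.5 and f = 0.70 it is 2.0 × (1 − 0.175) = 1.65 points. If loss depends on early feeding itself rather than on the later endline answer, more is recovered.

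**6. Precision.** The approximate variance ratio against endline data alone is 1 − r² × 0.2f ÷ (0.8 + 0.2f). At f = 0.20 and r = 0.5 the standard error falls by 0.6%; at f = 0.70 and r = 0.9 it falls by 6.2%. Power for 58% against 63%, with 4000 ÷ 1.25 = 3200 effective women, moves from 82.5% to between 82.9% and 87.0%.

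**The case against.** The strongest reply is that the quoted sentence says how dropout will be assessed, not how missing outcomes will be handled. Imputation models and auxiliary variables are commonly left to the statistical analysis plan, which the article mentions and which is not shown. A baseline comparison followed by a sensitivity analysis is conventional. This stands in part. A reader might infer that the trial will ignore outcome data it holds, or will use baseline characteristics and nothing else. The document supports neither: the word only is absent, and a mainly reliability purpose for the phone data does not exclude others. What remains is that the article names a specific set of variables, and a more informative one is planned in the same trial.

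A second reply is that phone data cannot rescue every primary outcome. This stands. A reader might infer that a woman who answers by phone and is then lost is no longer missing. That holds for early initiation, subject to agreement between the surveys. For exclusive breastfeeding it holds only if she has already stopped. The phone survey is not stated to cover contraception.

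A third reply is that 70% availability is optimistic. This also stands. Calling until 3500 is reached favours women who can be reached. A 35% phone-number loss would leave 5000 × 0.65 = 3250 women, below the target, and Table 2 assumes a 20% response rate for the related validation survey. Women lost at endline may be the same women who cannot be reached by phone.

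**Conclusion.** The point holds as an improvement to a stated method, not as the correction of an error. For the breastfeeding outcomes, dropout is to be judged on variables recorded before the outcome could occur, while planned post-birth data on breastfeeding have no stated role in missing data.

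The main gain is against bias, and it is partial: from an assumed 2.0 points to about 1.1 if 70% of lost women have phone data and about 1.5 if 35% do, with more left if fewer do or if the phone answer predicts less well. These figures rest on an assumed 10-point gap in one arm, an assumed share with phone data and an assumed 9% disagreement; the documents give none of the three. The precision gain is modest, roughly 1 to 6% off the standard error, and would not by itself justify the change. The comparison of women later seen with women later lost is useful even where the imputation recovers little, because it gives the sensitivity analysis an empirical starting point.

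**What to change.** First reconcile phone-survey coverage (3500 or all women) and timing (1 month, 6–8 weeks or 1–4 months) across Measurement, Study aim 1 and Table 2. Then amend the missing-data sentences in Analyses, for the breastfeeding outcomes only:

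- (a) Compare phone-reported breastfeeding, by arm, between women later seen and women later lost at endline.
- (b) Add an imputation analysis of missing endline breastfeeding that includes arm, stratifiers, baseline factors and the phone answers, calibrated in women with both surveys. For exclusive breastfeeding, treat the phone answer as a predictor, settling the outcome only where the woman has already stopped.
- (c) Use the gap found in (a) to set the range of the bias sensitivity analysis.

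Keep the baseline comparison for contraception.

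The cost is a little more analysis of data already planned, with no new contacts. There are two drawbacks: phone and face to face answers may differ, and women lost at endline may also be hard to reach by phone, so the number of lost women with phone data should be reported by arm.
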